### Elimination criteria

Trial participants will be allowed to or will be asked to leave the trial if (1) a participant has been included in the trial but cannot, at any stage in the trial, be subjected to the assigned treatment for various reasons, (2) severe adverse events occur that necessitate the withdrawal of a participant from the trial, (3) a participant does not fully participate in treatment or follow-up, (4) a participant does not match the inclusion criteria but has been accidentally included, and (5) a participant does not comply with the treatment or fails to provide information that may be important to the evaluation.

### Ethics

This trial has been approved by the Ethics Committee of the Institute of Shanghai General Hospital, Shanghai Jiao Tong University School of Medicine ([2017]31), Shanghai Municipal Hospital of Traditional Chinese Medicine (2017SHL-KY-06), and Shanghai Research Institute of Acupuncture and Meridians (2017–037-01). After obtaining ethics committee approval, the trial was registered on an authoritative registration platform for clinical trials (Acupuncture and Moxibustion Clinical Trial Registry, AMCTR-ICR-18000179). The informed consent form was developed in accordance with the Declaration of Helsinki.

Research assistants will thoroughly explain the purpose, procedure, treatment, and possible risks of the trial to participants, and they will clearly inform participants of their right to discontinue the trial at any point. Participants will be required to sign the informed consent form before the start of the trial. Research assistants will be in charge of the storage of all informed consent forms.

This is the protocol of the second version (v2.0 dated June 19, 2017). Based on the first version, the exclusion criteria have been slightly modified. All protocol versions have been submitted to the ethics committees of the three hospitals. Approvals from the research ethics committee review boards have been retained by the ethics committees of the three hospitals.

### Randomization

Participants will be randomly assigned at a ratio of 1:1 to a treatment or control group. The randomization sequence was generated using block randomization with a table of randomization. The table contains, in a random order, all possible combinations of a small series of figures, and it assumes an equal probability of a participant being randomly assigned to the treatment or control group. The order of interventions assigned to each block is randomized. The process is repeated for consecutive blocks until all participants are randomized. While receiving the first treatment, participants will be given sequential treatment cards from independent researchers to ensure adequate concealment.

### Blinding

This will be a single-blind trial. All participants will be treated separately to prevent communication. Except acupuncturists, all relevant parties will be blinded to the intervention groups. Treatments will be administered by two acupuncturists using treatment patches prepared by operational assistants. Due to the nature of AAP, it is difficult to fully ensure blinding among participants allocated to either group. Participants will be required to wait for 120 min in a room, after which their treatment patches will be removed by research nurses. In addition, acupuncturists, operational assistants, and research nurses are instructed to not communicate with participants on any information that might alert them to which group they have been allocated. Participants will be informed that they have an equal chance of allocation to the treatment or control group before research participation. The participants will be blinded to the group they belong to because needle penetration is achieved in all cases. In addition, outcome evaluators and statistical analysts will be blinded to the groupings and will not be involved in any part of the treatments during trial to ensure no statistical bias in the results.

### Intervention

#### Treatment group

All licensed acupuncturists have completed at least 5 years of undergraduate education and are registered TCM practitioners. All research assistants and licensed acupuncturists involved in the trial will receive a 2-day training session prior to the start of the trial. Both treatments will comprise 12 sessions, each lasting for 30 min, administered regularly over a 4-week period. The licensed acupuncturists will provide AAP thrice a week for 4 weeks.

The treatment group will receive AAP. Disposable and sterile 0.25 × 40 mm acupuncture needles (Suzhou Tianxie Acupuncture Instruments Co., Ltd., Suzhou, China) will be used. Acupoints include Yintang (EX-HN3), Yingxiang (LI20), and Shangyingxiang (EX-HN8) as well as Feishu (BL13), Dazhu (BL11), Fengmen (BL12), Taiyuan (LU9), and Zusanli (ST36), which will be located according to World Health Organization (WHO) International Standard Acupuncture Points. Participants will be positioned in the seated position during treatment sessions. After routine skin sterilization, needles will be inserted using the neutral reinforcing–reduced manipulation technique. Each needle will be rotated until the participant experiences the qi sensations of soreness, heaviness, and distension. The complete AAP formula used in this trial is not publicly available, but the primary herbal ingredients include *Rhizoma corydalis*, *Semen sinapis*, *Ephedra sinica*, *Cortex cinnamomi*, *Euphorbia kansui*, *Syzygium aromaticum*, and *Asarum sieboldii* Miq. These herbs are processed into powder, proportionally mixed at a ratio of 2:2:1:1:1:1:1, and blended into fresh ginger juice to create an AAP ointment, which is then mechanically poured into tubes. The resulting AAP ointment is stored in a refrigerator at 4 °C. The AAP ointment and matching placebo are both manufactured by the Pharmaceutical Preparation Department of the First People’s Hospital Affiliated to Shanghai Jiaotong University, and both meet the regulatory guidance requirements issued by the China Food and Drug Administration. For each acupoint, approximately 3 g of ointment is squeezed by assistants onto a 6-cm-diameter circular fabric. For each participant, the following six acupoints will be used, which are located according to the WHO International Standard Acupuncture Points: Dazhui (GV14), Feishu (BL13), Dingchuan (EX-B), and Tiantu (CV22). The treatment procedure has been standardized at each center by advance training (Table 2).

**Table 2 Tab2:** Acupoints and needling procedure

Acupoints	Angle and direction	Depth (mm)
Yintang (EX-HN3)	Transversely, downward	13
Yingxiang (LI20)	Transversely, towards the root of nose	5
Shangyingxiang (EX-HN8)	Transversely, towards the nose	8
Feishu (BL13)	Obliquely	5
Dazhu (BL11)	Obliquely	5
Fengmen (BL12)	Obliquely	5
Taiyuan (LU9)	Straightly	5
Zusanli (ST36)	Straightly	13

#### Control group

The control group will receive shallow needling at sham Yintang (EX-HN3), sham Yingxiang (LI20), sham Shangyingxiang (EX-HN8), sham Feishu (BL13), sham Dazhu (BL11), and sham Taiyuan (LU9). Each of these acupoints is a nonacupoint located at a different physical location to the actual acupoints. The placebo ointment is composed of buckwheat powder and coke, resulting in an ointment appearing similar to the AAP ointment.

#### Concomitant care and intervention

In both groups, participants with severe symptoms will be allowed to use rescue medicine with documentation of the medication. The type of medicine, dosage, and usage will be recorded on diary cards for analysis. For more complicated chronic diseases, participants must continue to take their routine medication and to receive the necessary therapies. In their case reports, the research staff will record the names of these diseases and the names of medications and therapies used.

#### Discontinuation of the intervention

The intervention should be terminated in the case of severe adverse events, withdrawal of participants, and unpermitted medication use.

### Outcome measures

#### Baseline information

Demographic information will be collected using a custom-made, standardized survey form that includes the following items: center location, name, age, sex, address, telephone number, and employment. A custom-made form will be used to collect medical information including diagnosis, nasal mucosal examination result, allergen examination result, typical symptoms, occurrence time of symptoms, accessory examination of nasal mucosa and nasal sinus, relevant diseases (allergic asthma and allergic conjunctivitis), and medication history.

#### Primary outcome measure

Change in TNSS will be measured for each participant by comparing the baseline score with the score at the end of the 4-week treatment. TNSS is determined by the severity of rhinorrhea, nasal pruritus, nasal obstruction, and sneezing.

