**Fig. 1 Fig1:**
[figure not shown]
CONSORT flow diagram

To achieve the targeted enrollment of participants, clinical recruitment flyers will be placed at three hospitals. Clinical recruitment staffs are responsible for enrolling 120 participants with moderate-to-severe PAR. Participants will be screened based on inclusion and exclusion criteria. All participants will be briefed on the purpose, procedures, treatments, and possible risks of the trial; and will be clearly informed of their rights to discontinue participation at any point. Screening will take approximately 1 week. During this period, participants will be asked to complete questionnaires related to their symptoms. Once participants have signed consent forms, they will be randomized to receive 12 sessions of AAP or sham acupuncture and AAP for 4 weeks.

The trial design flowchart is presented in Fig. 1, and the trial design schedule is shown in Table 1.

**Table 1 Tab1:** Trial design schedule

Period	Screening	Baseline	Treatment(W1–4)		Follow-up(W5-M6)	
Time	W-1	W0	W2	W4	M3	M6
Eligibility	X					
Demography and medical history	X					
Physical examination	X					
Informed consent	X					
TNSS	X	X	X	X	X	X
VAS	X	X	X	X	X	X
TNNSS	X	X	X	X	X	X
Adverse event			X	X		
Medication use	X	X	X	X	X	X
Compliance			X	X	X	X

*TNSS* Total Nasal Symptom Score, *VAS* visual analog scale, and *TNNSS* Total Non-Nasal Symptom Score

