### Exclusion criteria

Participants will be excluded if they meet any of the following criteria: (1) does not meet the diagnostic criteria for PAR; (2) presence of rhinosinusitis, sinusitis, and nasal septal deviation as comorbidities; (3) presence of severe respiratory illness, circulatory disease, digestive disease, urinary system disease, hematologic disease, nervous system disease, endocrine disease, mental disorder, or malignant tumor as comorbidities; (4) underwent antibiotic treatments for upper respiratory tract infection or paranasal sinusitis in the 2 weeks prior to the start of the trial; (5) pregnant or lactating women; (6) presence of skin lesions or scars on the AAP acupoint; (7) particularly sensitivity to drugs or dressings; (8) pretreatment TNSS of < 4; and (9) presence of alcoholism, which cannot be terminated during the experiment.

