#### Data collection and management

The research staff will be responsible for the collection of baseline characteristic data and medical results during the screening period. For convenience, all participants’ scores, observation times, AE records, and safety assessments will be consolidated into a single CRF. CRFs must be filled out immediately and accurately after each piece of information is acquired. Participants are required to record in their daily diary any other medications they take during the trial period. Outcome evaluators will examine the outcomes at baseline, 2 weeks (within treatment), 4 weeks (end of treatment), 1 month (within follow-up), 3 months (within follow-up), and 6 months (end of follow-up). Data on nasal and non-nasal symptoms will be collected.

Data monitoring and management will be performed every 3 months by the Clinical Research Center of First People’s Hospital Affiliated to Shanghai Jiaotong University. The clinical research monitor will monitor medical practitioners to ensure all processes are correctly implemented. A data monitoring committee (DMC) has been established independent of the sponsor, and no conflict of interest exists. The DMC is responsible for monitoring trial progression and guaranteeing participant safety. Interim analyses and termination plans for the trial have not been specified, but if the DMC requests interim analyses, these will be supplied. Two assistants will enter all data into an electronic database by double data entry. The statistical manager will be responsible for source data organizing, coding, range checking for data values, and converting data to ensure data quality. The database will be locked after all data have been cleaned. If participants withdraw from the trial, the reasons should be detailed and the rate of withdrawal should be statistically analyzed.

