### Statistical analysis

#### Sample size calculation

The trial will test two groups in parallel. Sample size calculation was performed using SAS 9.3 (SAS Institute Inc., Cary, NC, USA) at the Clinical Evaluation Center of First People’s Hospital Affiliated to Shanghai Jiaotong University. The mean change in TNSS before and after treatment was used as the indicator of efficacy evaluation in sample size calculation. Other research has shown a mean TNSS change of 2.53 ± 4.74 after acupuncture treatment [22] and 2.75 ± 1.06 after AAP [35]. Based on these findings, the appropriate trial sample size with power of 80%, alpha value of 0.05, and acceptable delta value of 0.2 was calculated. The results show that a clinically important difference can be detected by a sample size with at least 49 in each group. Accordingly, this number was increased to 60 per group (a total of 120) to allow for a predicted 20% dropout rate.

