#### Baseline information

Baseline adjusted analyses will be provided for center and severity variables, and the baseline value of the corresponding outcomes will be assessed. Descriptive statistics will be used to compare baseline measures with participant characteristics. If an imbalance occurs in baseline characteristics between the two groups, analysis of covariance will be applied.

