#### Efficacy analysis

Efficacy data analyses will be conducted on an intention-to-treat population. All participants initially included in any group will be considered in statistical analysis. Analysis of efficacy will be performed per-protocol and will include all participants who complete the entire research. Descriptive statistics will be used to compare serum indicators between the two groups. Regarding the primary and secondary outcome measures, a two-sample *t* test or Wilcoxon rank-sum test will be used to compare differences between both groups from baseline to the end of treatment (*p* < 0.05 will be considered statistically significant). The mean and standard deviation values of these parameters will be reported. Regarding repeated measures data, repeated measures analysis of variance will be performed after meeting spherical symmetry requirements. SPSS 16.0 will be used for all statistical calculations.

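### TNSS is scored twice before treatment, but the screening-week score has no part in the efficacy analysis; adding it as a second covariate could modestly tighten the primary estimate

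*Protocol article*

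**What the plan says.** Table 1 marks TNSS, VAS and TNNSS at W-1 (Screening) and again at W0 (Baseline). The Design text agrees that symptom data are gathered in the screening week: "Screening will take approximately 1 week. During this period, participants will be asked to complete questionnaires related to their symptoms".

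The Primary outcome measure section uses one pre-treatment score: "Change in TNSS will be measured for each participant by comparing the baseline score with the score at the end of the 4-week treatment". The secondary TNSS changes (Secondary outcome measures) also start from a single baseline score, and Data collection and management lists one baseline assessment: "Outcome evaluators will examine the outcomes at baseline, 2 weeks (within treatment), 4 weeks (end of treatment".

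Under Efficacy analysis, "a two-sample *t* test or Wilcoxon rank-sum test will be used to compare differences between both groups from baseline to the end of treatment". The analysis subsection on baseline information mentions baseline-adjusted analyses and adds: "If an imbalance occurs in baseline characteristics between the two groups, analysis of covariance will be applied".

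The only visible use for a further pre-treatment score is eligibility. The exclusion criteria list "pretreatment TNSS of < 4" without naming the visit, and Table 1 places eligibility at screening.

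**The concern.** Both scores come before any needling or ointment, so either may be used for adjustment without compromising the randomised comparison. A TNSS reading at one visit carries visit-to-visit noise. A change score subtracts that noise at full weight, and adjustment for W0 alone removes only what that one noisy reading can explain. A second pre-treatment reading, already scheduled, may carry further information about the participant's underlying level.

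At stake is precision: the confidence interval for the primary effect may be somewhat wider than the scheduled data allow. The validity of the comparison is not at stake. The point concerns a stated method, since the article fixes both the single-baseline change and an unadjusted test of it.

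**Working it through.** **Inputs.** Two pre-treatment TNSS visits, W-1 and W0, and the primary visit W4 (Table 1). The article gives no correlation between visits, so every correlation below is an assumption. TNSS is scaled to SD 1 at each visit, with equal SDs. Write rb for the correlation of W-1 with W0, r0 for W0 with W4, and r1 for W-1 with W4.

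**The plan's own figure.** The article gives no variance or precision figure for this choice. The nearest is 49 per group under Sample size calculation, which its stated inputs do not reproduce. The changes 2.53 (SD 4.74) and 2.75 (SD 1.06) differ by 0.22. The pooled SD is √[(4.74² + 1.06²)/2] = 3.43. Then n = 2 × (1.960 + 0.842)² × 3.43² / 0.22², about 3,826 per group (two-sided, 80% power). That is a separate matter. It matters here because 49 cannot serve as the base for a sample-size saving.

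**Formulas.**
- Change from W0: 2(1 − r0).
- Change from the mean of W-1 and W0: 1 + (1 + rb)/2 − (r0 + r1).
- ANCOVA residual variance, W0 only: 1 − r0².
- ANCOVA residual variance, both as separate covariates: 1 − (r0² + r1² − 2·r0·r1·rb)/(1 − rb²).

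**Results.**

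| rb; r0; r1 (assumed) | Change score: W0 → mean of two | ANCOVA: W0 → both |
|---|---|---|
| 0.3; 0.3; 0.3 | 1.400 → 1.050 (25% lower) | 0.910 → 0.862 (5% lower) |
| 0.5; 0.5; 0.5 | 1.000 → 0.750 (25% lower) | 0.750 → 0.667 (11% lower) |
| 0.7; 0.7; 0.7 | 0.600 → 0.450 (25% lower) | 0.510 → 0.424 (17% lower) |
| 0.8; 0.5; 0.5 | 1.000 → 0.900 (10% lower) | 0.750 → 0.722 (4% lower) |
| 0.71; 0.61; 0.58 | 0.778 → 0.665 (15% lower) | 0.627 → 0.584 (7% lower) |
| 0.8; 0.5; 0.4 | 1.000 → 1.000 (no gain) | 0.750 → 0.750 (no gain) |
| 0.9; 0.66; 0.59 | 0.688 → 0.703 (2% higher) | 0.570 → 0.570 (no gain) |
| 0.9; 0.5; 0.4 | 1.000 → 1.050 (5% higher) | 0.750 → 0.737 (2% lower) |

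The fifth row assumes measurement noise plus decay, correlation = 0.75 × 0.95^weeks, at lags of 1, 4 and 5 weeks. The seventh is pure autoregressive decay of 0.9 per week. Both were computed from unrounded correlations.

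**Reading the table.** Averaging helps the change score only when r0 − r1 < (1 − rb)/2. If W-1 and W0 are closely correlated and W-1 predicts W4 noticeably less well than W0, averaging gains nothing or loses. For ANCOVA with both scores, the added value of W-1 is nil when r1 = rb × r0, the pure-decay case, and is never negative in residual variance.

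**In terms of the interval.** Width goes with the square root of the variance. A 5% to 17% fall in variance gives √0.947 = 0.973 to √0.830 = 0.911, an interval about 3% to 9% narrower.

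**The degree of freedom.** With 60 × 0.8 = 48 evaluable per arm, intercept, group and W0 leave 96 − 3 = 93 residual degrees of freedom. Adding W-1 leaves 92, a cost of roughly 1/92, or about 1%.

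**Keeping two gains apart.** Under equal correlations, moving from the change score to ANCOVA on W0 alone already lowers variance by (1 − r)/2: 35%, 25% and 15% at r = 0.3, 0.5 and 0.7. The ANCOVA column shows only what W-1 adds beyond that.

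**The case against.** The strongest case against is that nothing is misstated. Table 1 calls W0 the baseline and W-1 the screening visit, and the outcome and data-collection sections consistently use one baseline. The last pre-treatment visit is the conventional choice, and the screening score has its own purpose in eligibility. Baseline-adjusted analyses are already mentioned, and a detailed statistical analysis plan is announced that could hold a second covariate. All of this stands as to error: there is none. It does not dispose of the point, because the article itself fixes the single-baseline change and an unadjusted t or Wilcoxon test, with ANCOVA tied to observed imbalance.

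The objection to the size also stands. A reader might infer that a quarter of the variance is being thrown away, equivalent to 64 instead of 48 participants per arm (48/0.75 = 64). That holds only if W-1 and W0 correlate with each other no more strongly than either does with W4. The documents do not say so, and scores one week apart would usually correlate more strongly than scores four or five weeks apart.

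A reader might also infer that a noisy W0 reading biases the treatment effect. It does not: the noise is random and randomisation balances it in expectation.

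Averaging has a further drawback. If the eligibility threshold is applied to W-1, putting that selected score into the baseline adds regression to the mean to the within-arm changes, although not to the contrast between arms.

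**Conclusion.** The point holds as a modest, optional efficiency gain. The W-1 TNSS is scheduled and has no stated efficacy role. Used as a separate covariate alongside W0, it would lower residual variance by about 5% to 17% under assumed equal correlations of 0.3 to 0.7, about 7% under the noise-plus-decay illustration, and about 0% under pure autoregressive decay, before a cost of about 1% for the degree of freedom. These figures assume equal SDs at each visit and correlations that the documents do not supply.

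Averaging the two scores is not supported as the remedy, since its effect runs from 25% lower variance to about 5% higher. No sample-size saving follows, both because the correlations are unknown and because the stated 49 per group does not follow from its inputs.

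**What to change.** Prespecify the primary comparison of week-4 TNSS, or of its change from W0, as an ANCOVA with W-1 and W0 TNSS entered as separate covariates, whether or not imbalance is seen. With W0 in the model, the two outcome forms give the same treatment estimate. Where W-1 is missing, use the multiple imputation already planned. Do the same for VAS and TNNSS, which are scheduled at the same two visits. Keep W0 as the baseline for descriptive change scores.

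Separately, state which pre-treatment TNSS the exclusion threshold refers to; that is for the sponsor to clarify.

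The cost is one sentence on the model, one degree of freedom per analysis and a clarification of the exclusion criterion. No visit or measurement is added, so it can still be done although recruitment has begun, provided it is fixed before unblinding.
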